## Abstract

**Background:**

Hypertension  (HTN) affects approximately 25% of the UK population and is a leading cause of mortality. Associated annual health care costs run into billions. National treatment guidance includes initial lifestyle advice, followed by anti-hypertensive medication if blood pressure (BP) remains high. However, adoption and adherence to recommended exercise guidelines, dietary advice and anti-hypertensive medication is poor. Four short bouts of isometric exercise (IE) performed 3 days per week (d/wk) at home elicits clinically significant reductions in BP in those with normal to high-normal BP. This study will determine the feasibility of delivering personalised IE to patients with stage 1 hypertension for whom lifestyle changes would be recommended before medication within NHS primary care.

**Methods:**

This is a randomised controlled feasibility study. Participants were 18+ years, with stage 1 hypertension, not on anti-hypertensive medication and without significant medical contraindications. Trial arms will be standard lifestyle advice (control) or isometric wall squat exercise and standard lifestyle advice. Primary outcomes include the feasibility of healthcare professionals to deliver isometric exercise prescriptions in a primary care NHS setting and estimation of the variance of change in systolic BP. Secondary outcomes include accuracy of protocol delivery, execution of and adherence to protocol, recruitment rate, attrition, perception of intervention viability, cost, participant experience and accuracy of home BP. The study will last 18 months. Sample size of 100 participants (50 per arm) allows for 20% attrition and 6.5% incomplete data, based upon 74 (37 each arm) participants (two-sided 95% confidence interval, width of 1.33 and standard deviation of 4) completing 4 weeks. Ethical approval IRAS ID is 274676.

**Discussion:**

Before the efficacy of this novel intervention to treat stage 1 hypertension can be investigated in any large randomised controlled trial, it is necessary to ascertain if it can be delivered and carried out in a NHS primary care setting. Findings could support IE viability as a prophylactic/alternative treatment option.

**Trial registration:**

ISRCTN13472393, registered 18 August 2020

**Supplementary Information:**

The online version contains supplementary material available at 10.1186/s40814-021-00925-w.

## Introduction

### Background and rationale

Hypertension (≥ 140/90 mmHg) [1] affects approximately 1 in 4 people in the UK and is a leading modifiable risk factor for mortality [2]. As the most common long-term health condition in the UK and a primary risk factor for mortality [2], hypertension is a serious health problem [3, 4]. With every 20 mmHg increase in systolic BP above 115 mmHg and 10 mmHg increase in diastolic BP above 75 mmHg, the risk of mortality from cardiovascular disease doubles [5]. Public Health England (PHE) suggests that there is an opportunity to prevent more than 9000 heart attacks and at least 14,000 strokes over 3 years with better detection and management of high BP, high cholesterol and atrial fibrillation [6]. Estimates indicate that the annual burden from conditions attributable to hypertension is over £2 billion in England [4], with long-term care following a debilitating heart attack, stroke and/or vascular dementia often precipitated by hypertension costing substantially more [7, 8]. It has been suggested that over ten years, 45,000 quality adjusted life years and £850m could be saved if England achieved a 5 mmHg reduction in population systolic BP [4, 8]. In 2007, the NHS and PHE announced a drive to prevent thousands of heart attacks and strokes but highlighted the need for research into innovative lifestyle modifications to lower BP [4]. New personalised support for lifestyle changes [3], like our IE training prescription [9, 10], delivered by primary care allied health professionals could support this drive without directly adding to GP workload [11].

#### Standard care for hypertension

National guidance for the treatment of hypertension is graded from lifestyle intervention (i.e. advice about diet, weight management, exercise, alcohol intake) to pharmacological therapy depending upon severity and duration of hypertension when other factors have been taken into account such as age, co-morbidity and the presence of target organ damage [1, 12]. The goal of antihypertensive therapy is generally to reduce clinic BP to < 140/90 mmHg, although recommended targets vary depending on age and co-morbidity [1, 13]. However, up to 50% of people fail to achieve their target BP [14, 15] mainly due to non-compliance (estimated 30–50% failing to comply at 6 and 12 months, respectively) [16, 17] with undesirable side effects of anti-hypertensive medication often cited in this context [18, 19].

#### Lifestyle interventions

The importance of lifestyle changes to aspects, such as diet and exercise habits for patients with hypertension in the absence of other risk factors should not be overlooked [1, 20]. Additional treatment options are also in keeping with the UK government’s commitment to provide greater patient choice [21]. Whilst dietary strategies can be effective, these are difficult to fully adopt and maintain [22, 23].

Evidence suggests that exercise may be as effective as medication in controlling BP [24–26] and it is often promoted as a treatment option for those with stage 1 hypertension (defined as a blood pressure of 140–159/90–99 mmHg), without co-morbidity or other long-term conditions [1, 27]. Current exercise guidelines for the prevention and treatment of hypertension recommend that adults accumulate a mainstay of 30+ min of moderate intensity aerobic exercise on 5, but preferably all, days per week (d/wk), supplemented by moderate to vigorous resistance exercise 2–3 d/wk and general flexibility exercise ≥ 2–3 d/wk [28, 29]. However, in a randomised controlled trial, a long-term programme of aerobic exercise training failed to reduce clinic BP [30]. This may be due to poor adherence (e.g. 67%) to the relatively high amounts of aerobic exercise recommended [30, 31]. Furthermore, other studies have demonstrated attrition rates as high as 50% during traditional aerobic exercise interventions [32, 33]. Indeed, evidence typically suggests that a significant challenge is the low adoption and high attrition rates associated with these guidelines [34]. Thus, effective and manageable lifestyle interventions with respect to exercise remain an unmet clinical need [3]. It is suggested that to promote lifestyle exercise changes, patients need easily adopted, effective and manageable exercise interventions as a first line option for managing their BP.

#### Isometric exercise

Meta-analyses indicate that isometric exercise (IE) results in larger reductions in BP when compared with either aerobic and dynamic resistance exercise training [25, 35] and has great potential to treat hypertension [10, 36] and improve cardiovascular health, which may reduce mortality risk [37]. We have shown that IE can lower BP in people with both normal [9, 38] and high-normal (pre-hypertensive) [10, 39] BP and therefore has the potential to be an effective lifestyle intervention for hypertension. IE involves holding a fixed position for a period of time; skeletal muscles are used but there is no movement, e.g. the wall squat which involves leaning against a wall in a seated position (Fig. 1).

**Fig. 1 Fig1:**
[figure not shown]
Isometric wall squat exercise

Evidence suggests that IE offers distinct advantages over other forms of exercise [10, 36] making it a better lifestyle treatment for hypertension. A frequently cited barrier to exercise is lack of time [40, 41]. Though aerobic exercise guidelines recommend ≥ 150 min/week [42], it has been demonstrated that adherence is better with shorter bouts of exercise [43, 44]. Only 24 min of isometric wall squat exercise a week are required to achieve clinically significant reductions in BP of 12/6 mmHg in pre-hypertensives [10]. Moreover, our evidence-based IE wall squat programme can be easily prescribed by health care providers and is very simple to execute regardless of age or physical ability [10, 45]. It does not require costly equipment or access to specialist facilities, does not require specific clothing, and most importantly, is easily performed at home [9, 10]. Empowering patients to manage their condition is key and use of short, simple, personalised exercise that can be carried out at home may enable this [46, 47]. Furthermore, our personalised exercise ‘prescription’ ensures optimal IE intensity is achieved, helping to improve confidence, motivation and patient adherence [40, 48].

### Contextualising current findings

The importance of these findings is substantial [49] considering a 10 mmHg reduction in systolic BP and 5-mmHg reduction in diastolic BP is associated with a 40% lower risk of stroke and 30% lower risk of mortality from heart disease and other vascular causes throughout middle age [6]. Although we have consistently demonstrated that IE can lower BP [10, 37, 38, 50], interpretation of the results, along with the findings of others is limited by small participant numbers [9, 10, 37, 51–56]. Isometric exercise may provide a new viable solution with respect to exercise for those with stage 1 hypertension, but evidence for the efficacy of IE in this clinical population is still not robust. Furthermore, this intervention has never been tested within a NHS setting, nor confirmed in any large randomised control trials. This feasibility study was deemed necessary by the NIHR to determine uncertain parameters necessary to inform and justify the design and further funding of a large scale randomised controlled trial to evaluate the efficacy and mechanisms of isometric wall squat exercise to lower BP in stage 1 hypertensive NHS patients.

## Objectives

The aim of the study is to determine the feasibility of delivering an individually tailored IE training programme to patients with stage 1 hypertension (defined as a clinic BP of 140–159/90–99 mmHg) for whom lifestyle changes would be recommended before pharmacological treatment within a primary care NHS setting. Furthermore, the primary objectives are as follows:To assess if healthcare professionals (e.g. nurses, health trainer, healthcare assistants, physiotherapists) can deliver isometric exercise prescriptions for stage 1 hypertensive patients in a primary care NHS settingTo estimate the variance in BP change, to enable sample size calculation for a definitive randomised controlled trial

The secondary objectives are as follows:Evidence the fidelity of the study intervention with respect to healthcare professional delivery and patient completion of IEEstimate short- (4 week) and medium-term (3 and 6 month) adherence rates to IE interventionEstimate recruitment and attrition rates at recruiting GP sites to inform future trialsExplore the willingness of GPs, secondary care clinicians and healthcare professionals to consider IE as a treatment option for patients, including barriers and facilitators for delivering and integrating this within an NHS care pathway for hypertensionEstablish the cost and cost-utility of the IE intervention compared to standard care for stage 1 hypertensionUnderstand participant experiences of undertaking IE, adherence to the programme and continuation. Additionally, explore possible negative effects of COVID-19 on recruitment rates and participationTo investigate the feasibility of using observed home blood pressure readings for remote monitoring

## Trial design

### Design

Multi-centre randomised controlled feasibility study.

### Random allocation

Those that meet the inclusion criteria will be randomised to one of two groups in a 1:1 ratio. One hundred participants will be recruited; therefore, 50 participants will be allocated to each group.

### Amendments due to COVID-19 pandemic

As a result of the unprecedented spread of a novel coronavirus early in 2020, by mid-March the European region had become the epicentre of a COVID-19 pandemic [57]. An outcome of this was that many recently funded health projects using human participants, including this study, were required to re-evaluate their viability and where necessary revise their research design, methods and protocols in line with general Government and specific funder guidance (e.g. NIHR Restart Framework [58]) to help ensure the continued safety of research participants and personnel alike. The main changes made to this study are documented (*identified in italics*) to provide the reader with greater insight into how this research project evolved to become fit for purpose as part of what has now become a new research normal.

## Methods: participants, interventions and outcomes

### Study setting

GP practices in the South East of England.

### Eligibility criteria

Patients aged 18+ with stage 1 hypertension who are not yet on anti-hypertensive medication and without any significant medical condition that would contraindicate their participation.

### Exclusion criteria

Patients who are taking anti-hypertensive medication; have white coat hypertension (as evidenced by averaged home systolic BP < 135 mmHg); are unable to undertake the study intervention (isometric exercise); have a previous history of diabetes mellitus (type 1 or type 2), known or suspected ischaemic heart disease (including myocardial infarction and/or angina and/or coronary revascularization procedure), moderate or severe stenotic or regurgitant heart valve disease, atrial or ventricular arrhythmia, stroke or transient ischaemic attack, aortic aneurysm and/or peripheral arterial disease, uncorrected congenital or inherited heart condition; have an estimated glomerular filtration rate < 45 ml/min (calculated using CKD-EPI or MDRD formulae, and taking most recent documented results); have a documented left ventricular ejection fraction < 45% and/or left ventricular hypertrophy (by either echocardiography or standard ECG criteria, e.g. Sokolow-Lyon); have a documented urine albumin to creatinine ratio > 3.5 mg/mmol; are unable to provide informed consent; are enrolled in another Clinical Trial of an Interventional Medicinal Product or Medical Device or other interventional study; and if female, are pregnant or currently breast feeding. Then finally, any medical condition that, in the opinion of the investigator, would make the participant unsuitable for the study.

### Who will take informed consent?

Trained healthcare professionals will be obtaining informed consent via discussion on *video call and completion via online software* or hardcopy.

## Interventions

### Explanation for the choice of comparators

National guidance for patients newly diagnosed with stage 1 hypertension is two tiered and recommends that GP’s normally provide advice about potential lifestyle (non-pharmaceutical) changes that may help to reduce BP in the first instance before prescribing antihypertensive medication [1]. As such, the comparator used in this study will be defined as ‘standard care lifestyle advice’. One potential issue raised during preliminary consultation with PPI members, the healthcare professionals (including GP’s) in primary and consultants in secondary care was related to the concept of standard care lifestyle advice. It quickly became evident that there are differences in the quality and consistency of standard care lifestyle advice provided by primary care centres across the region (and indeed the UK). As such, it was agreed by the Project Management Group that for accurate comparison of the intervention (arm 1) with the control (arm 2), standard care lifestyle advice would need to be as consistent as possible across participating sites. The best way to achieve this within the project time frame was to adhere to common published guidelines that would be given to all HCP’s and patients involved. As such, the project adopted an existing peer reviewed leaflet produced by the East Kent Hospitals University NHS Foundation Trust (EKHUFT) entitled: High Blood Pressure (Hypertension) - Information for Patients from the Department of Renal (Kidney) Medicine.

### Intervention description

Standard care lifestyle advice (arm 1 — control) or isometric wall squat exercise training with standard care lifestyle advice (arm 2). Figure 2 shows flow-chart of selection of participants and interventions.

**Fig. 2 Fig2:**
[figure not shown]
Trial flow chart

The following lifestyle information will be provided to all participants taking part in the study.Lifestyle changes that are recommended for people with high blood pressure include the following:Salt intake. The average salt intake in the UK is 9 g/day. The recommended daily salt intake for an adult is 5 to 6 g/day. Reducing the amount of salt in your food lowers blood pressure and makes blood pressure lowering medications more effective. Although stopping adding salt to your food when cooking or at the table is important, 80% of the salt we eat is already present in food when we buy it — so called ‘hidden salt’. Understanding food labelling can help you see where these hidden sources of salt are found.Healthy diet. You should follow a diet that is rich in fresh fruit and vegetables and low in saturated fat.Weight. You should try to maintain a body mass index between 20 and 25 kg/m^2^. Those with BMI greater than 30 kg/m^2^ and high blood pressure should definitely try to lose weight to achieve a BMI of 30 kg/m^2^ or below. See BMI chart at the end of this leaflet.Alcohol consumption. You should adhere to the current UK limit of less than 14 units per week. If you do regularly drink as much as 14 units in a week try to spread your drinking evenly over three days or more. One unit of alcohol is equivalent to half-pint of average strength beer, a small glass of wine (125 ml), or a single pub measure of spirits. Remember that stronger beers (such as continental lager) and larger glasses of wine (175 ml or 250 ml) will contain more units.Exercise. You should try to exercise at a level that makes you breathless for at least 30 min three times a week, although more is recommended if possible. A variety of different types of exercise — aerobic/endurance (for example running) and resistance (for example weights) — both appear to be equally helpful in reducing blood pressure.For more information on lifestyle modification visit the Blood Pressure UK website:www.bloodpressureuk.org/BloodPressureandyou/Yourlifestyle

The full leaflet ‘High Blood Pressure (Hypertension) - Information for Patients from the Department of Renal (Kidney) Medicine’ is presented as an additional file (see Additional file 1).

Participants allocated to the intervention arm 2 will be required to attend their GP surgery to perform an incremental isometric wall squat test. This test will be delivered by the designated healthcare professional (HCP) previously trained in the delivery of this protocol. Upon arrival participants will be familiarised with a simple rating of perceived exertion scale validated specifically for use with isometric exercise [59]. Following this, they will be fitted with a wireless heart rate monitor chest strap and wrist watch (Sigma PC 15.11, Neustadt/Weinstraße, Germany) and MIE clinical goniometer (MIE Medical Research Ltd., Leeds, UK), which will be attached to the participant’s left leg using elastic Velcro straps. The fulcrum will be aligned with the lateral epicondyle of the femur, and the moving arm is placed on the lateral midline of the femur using the greater trochanter for reference and the stationary arm on the lateral midline of the fibula using the lateral malleolus and fibular head for reference. A spirit level will be attached to the stationary arm to ensure that the lower leg is kept vertical during exercise (Fig. 3) [37].

**Fig. 3 Fig3:**
[figure not shown]
Goniometry of the knee

The participant will then be asked to perform a continuous isometric wall squat test in stages of increasing intensity, which is determined by manipulating knee joint angle with the internal angle between the femur and fibula measured. Based upon the work of Goldring et al. [53], the first stage begins at 135° of knee flexion, and participants are instructed to hold this position for 2 min. HR is measured continuously throughout the incremental test with HR recorded every 5 s during the last 30–0 s of each 2-min increment. Wall (measured as floor to coccyx height) and floor (measured as wall to back of the heels) positions are also recorded (cm) in the final 10 s of each increment. At the end of each increment, participants will be asked to rate their perceived exertion to give the healthcare professional an indication of how close they are to finishing the test. Once each stage is complete the knee joint angle will be decreased by 10°. The angle is then decreased every 2 min until the participant reaches the end of the 95° stage or can no longer maintain the knee joint angle within 5° of the target value (volitional fatigue). The HCP’s were instructed to maintain a good dialogue (providing as much encouragement as was necessary) with the participant throughout, to ensure they stay calm and relax their breathing to avoid the Valsalva manoeuvre, to watch closely for any signs of physical distress and not to hesitate to stop the test immediately if they feel the participant’s health is at risk [60].

Based upon each participant’s test data, knee joint angle is plotted against the mean HR for the last 30 s of each incremental stage. Since an accurate IE wall squat prescription requires data from at least 3 complete stages, any participant unable to achieve this will be classed as a screen failure and informed that they will not be able to take part in the study. The relationship between parameters is then used to calculate the specific knee joint angle required to elicit a target HR. The target HR selected for training is 95% HR_peak_, with HR_peak_ defined as the mean HR of the final 30 s achieved during the incremental test [60]. Additionally, the individual target heart rate range (THRR) will be established using the 95% reference interval [61].

During the 10-min data analysis period (performed remotely by the study research assistant), the patient will be taken through the participant information and their personal IE training diary (used to record the HR and RPE data from each training session performed in the home) to ensure that they fully understand what is required of them throughout the 6-month training period. At this stage, the patient will also be issued with their own HR monitor, shown how to work it and given a written instruction sheet for future reference.

A goniometer is not deemed practical for participant measurement of knee joint angle during home-based training; therefore, a simple device called the ‘Bend and Squat’ is used to align a participant’s feet and back into the correct position for a given wall squat knee joint angle (Fig. 4) [55].

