### Participant timeline

The participant timeline is presented in Table 1.

**Table 1 Tab1:** Participant schedule of events

Assessment	Remote screening assessment day 14	Study time point					
		Baseline assessment day 1 (remotely)	IIET visit (within 7 days of Baseline visit)	Follow up telephone call — IE arm only (within 7 days of IIET visit)	Assessment 2 day 28–33 (remotely)	Assessment 3 month 3 (± 7 days) (remotely)	Assessment 4 month 6 (± 7 days) (remotely)
Medical history	X	X					
Concomitant medication	X	X		X	X	X	X
Consent	X						
Observed blood pressure and heart rate		X			X	X	X
IE ability test	X						
Incremental IE test and IE programme provided (for those randomised to intervention arm only)			X				
AE review				X	X	X	X
Diet questionnaire		X			X	X	X
Exercise questionnaire		X			X	X	X
Quality of life questionnaire		X			X	X	X
Collection of IE exercise diary (for those randomised to intervention arm only)				X	X	X	X
Collection of home blood pressure and heart rate readings	X (between day 7 and day 1)	X		X	X	X	X
Health resource use questionnaire					X	X	X
IE experience questionnaire					X		

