Accuracy of IE protocol delivery will be determined using data from three fidelity assessments; the first being healthcare professional competency checks administered during their isometric exercise prescription training; the second being expert observation/evaluation of at least the first IIET delivered by each HCP; and then finally, by third party examination of the first week of heart rate data recorded in the study diaries of each HCP’s specific participants, with average HR calculated from the first 3 sessions being compared against the individuals target training HR as described above.

Execution of the IE training protocol in the home will be assessed for each individual participant at the end of the first week by checking to see if their mean training heart rate per week falls within target heart rate range/reference interval (76–111%) *data for weeks 4, 12 and 24 will now be assessed at the end of the 6-month training period*. An estimate of the short- (4 week) and medium-term (3 and 6 month) adherence rates to IE training will be based upon the data collected from participant diaries to calculate the proportion of participants completing ≥ two thirds of all IE sessions (12, 36 and 72) at each time point respectively. Patient recruitment and participant attrition rates will be calculated based upon the average number of participants recruited per week over the 7 month recruitment period and the number of withdrawals from the study once the last follow-up call to the last participant has been made.

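### Exercise-arm participants who cannot complete three stages of the incremental test are removed after randomisation as screen failures, while controls never face the test

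*Protocol article*

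**What the plan says.** Under Random allocation, eligible people are "randomised to one of two groups in a 1:1 ratio", and "One hundred participants will be recruited; therefore, 50 participants will be allocated to each group". Eligibility is therefore settled before allocation.

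The incremental test comes afterwards. In Intervention description, where arm 2 is the exercise arm: "Participants allocated to the intervention arm 2 will be required to attend their GP surgery to perform an incremental isometric wall squat test". Table 1 (Participant timeline) agrees. The row reads "Incremental IE test and IE programme provided (for those randomised to intervention arm only", and the column is headed "IIET visit (within 7 days of Baseline visit".

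The same description then says that an accurate prescription needs at least three complete stages, and that "any participant unable to achieve this will be classed as a screen failure and informed that they will not be able to take part".

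Two ability checks apply to both arms before randomisation. Exclusion criteria rules out people who cannot do the exercise, and Table 1 lists an IE ability test at remote screening. Neither is described as the three-stage requirement.

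**The concern.** A randomised participant cannot be a screen failure. The label treats the removal as if it came before allocation, when in fact it follows allocation and applies to one arm. A control with the same limited capacity is never tested and stays in.

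Two results are exposed. The first is the treatment difference in systolic BP change with 80% and 95% confidence intervals. It is listed under primary outcomes and is meant to inform whether to proceed to a confirmatory trial. If the rule removes people from one arm by physical capacity, the comparison is no longer fully protected by randomisation. The ANCOVA adjusts for baseline, centre, sex and age, not for wall squat capacity.

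The second is the feasibility evidence. The first primary objective asks whether professionals can deliver exercise prescriptions. A participant for whom no prescription can be made bears directly on that question, yet no listed outcome clearly counts such a person.

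**Working it through.** **1. The plan's own figures.** The sample size section gives a 95% interval of width 1.33 at SD 4 and n = 74. This is a chi-square interval for one SD: limits 4 × √(73/χ²), with the 97.5% and 2.5% points on 73 degrees of freedom. They are 3.443 and 4.773, so the width is 1.330, as stated. Completers from 100 recruited: 100 × (1 − 0.265) = 73.5, or 100 × 0.80 × 0.935 = 74.8; the plan's 74 is consistent with both. The sample size calculation is sound, and this point does not depend on it.

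**2. Order of events.** Eligibility, then 1:1 randomisation (Random allocation); then the incremental test in the exercise arm only (Intervention description, Table 1); then removal if fewer than three stages are complete. The selection acts after allocation, on one arm.

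**3. Effect on the treatment difference.** Let f be the share of the exercise arm failing the rule, and D the difference in mean BP change between those who pass and those who fail.

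- Mean over all randomised to exercise: (1 − f) × m_pass + f × m_fail
- Mean after removal: m_pass
- Shift: f × (m_pass − m_fail) = f × D

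The documents give neither f nor D. I assume f = 5–20% and D = 5 mmHg. The two right-hand columns also assume that the failures come on top of the stated losses and are not replaced.

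| f | Removed of 50 | Shift at D = 5 mmHg | Exercise completers, 37 × (1 − f) | Width of SD interval |
|---|---|---|---|---|
| 0 | 0 | 0 | 37 | 1.33 |
| 5% | 2.5 | 0.25 | 35.2 | 1.35 |
| 10% | 5 | 0.50 | 33.3 | 1.37 |
| 20% | 10 | 1.00 | 29.6 | 1.40 |

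For scale, the standard error of a simple difference at SD 4 and 37 per arm is 4 × √(2/37) = 0.93 mmHg. That is my derivation; the protocol plans no such figure. The loss of precision is minor, so the issue is comparability.

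**4. Does the intention-to-treat analysis repair it?** The missing-data section names intention to treat only as a secondary analysis, with baseline carried forward when nothing else is available. It does not say that people classed as screen failures belong to it. If they did, but were not followed up, the method would enter a change of zero for each. That is an imputed value, not an observed outcome.

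**5. Are they counted elsewhere?**
- Attrition is based on "the number of withdrawals from the study once the last follow-up call to the last participant has been made"; whether a screen failure is a withdrawal is not said.
- Adherence is a proportion drawn from training diaries, with no stated denominator.
- Heart-rate fidelity rests on training sessions, which these people never have.
- Delivery by professionals is judged by competency checks, observation of at least each professional's first test, first-week heart rates and focus groups.

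To show what the open denominator can do: if two thirds of those remaining adhered (an illustrative value), the proportion of all randomised to exercise would be 2/3 × 0.90 = 60% at f = 10%, and 2/3 × 0.80 = 53% at f = 20%.

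**The case against.** The strongest reply is that both arms have already been screened for ability, so few should fail later. This stands in part: those checks should lower f, and the extra selection may be modest. But they are not stated to be the three-stage criterion, and the later rule would be unnecessary if they were sufficient.

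Second, this is a feasibility study and the BP difference is described as preliminary. That limits the severity, but the estimate is still a listed primary outcome meant to inform the decision to proceed.

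Third, a reader might infer that failed prescriptions disappear from the feasibility results, or that a delivery rate of 40 out of 50 would be reported as 40 out of 40. The documents do not support either. No section says these participants leave any denominator, and no patient-level delivery rate is defined; the listed outcomes for that objective are qualitative. Failures could also emerge in observed tests, focus groups or a participant flow count. What stands is narrower: no listed outcome clearly counts them. The trial flow chart (Fig. 2) was not visible in the text available to me and should be checked.

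Finally, an analysis plan could settle denominators and analysis sets. It could not recover BP readings never collected because participation had ended.

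**Conclusion.** The exclusion is real and is written into the protocol: it follows randomisation and applies to the exercise arm only. Its size and direction are unknown. Under the assumptions above (f = 5–20%, D = 5 mmHg) the shift in the BP difference is 0.25 to 1.0 mmHg, roughly a quarter of the derived standard error up to about equal to it. With f near zero it would be negligible.

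It would go too far to say that the comparison is certain to be materially biased, or that feasibility is certain to be overstated. The first rests on assumed values of f and D, and the second on denominators that the article leaves open. Severity: should-fix. The sections conflict, and the follow-up lost under the rule cannot be recovered at analysis.

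**What to change.** Reconcile the three-stage rule in Intervention description with Random allocation and Table 1:

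- Do not class randomised participants as screen failures. Who receives a prescription does not change.
- Keep those without a prescription in the study and collect their scheduled BP assessments at 4 weeks, 3 months and 6 months, which are already remote.
- Analyse them in the arm to which they were randomised.
- Report the number with no deliverable prescription out of all randomised to exercise, and count them as not adherent.

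The cost is a change to the protocol and participant information, follow-up of a few more people, and slightly less favourable feasibility and adherence figures.

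An equivalent test in both arms before allocation would also remove the asymmetry. It would add a surgery visit for every candidate and restrict the trial to those who pass, so retention is the lighter change.
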